#### Sample size calculation

The treatment effect size is unknown and therefore cannot be used to inform sample size calculations. A sample size of 60 has been selected pragmatically based on feasibility of recruitment.

However, longitudinal clinical data from the Incidence of Cognitive Impairment in Cohorts with Longitudinal Evaluation-PD (ICICLE-PD) cohort study provides some idea of an anticipated effect size for the primary outcome measure. ICICLE-PD patients were stratified by cytokine profile. Those with a ‘proinflammatory’ profile (n=32) had a more rapid symptom progression, with mean (SD) annualised change in MDS-UPDRS gait/axial score of 1.95 (1.92). In the subgroup with an ‘anti-inflammatory’ cytokine profile (n=26), mean (SD) annualised change in MDS-UPDRS gait/axial score was 0.72 (1.40).^12^ The corresponding between-group difference of 1.2 points is equivalent to a standardised effect size (Cohen’s d) of 0.73. The magnitude of this effect, which equates to a 4% change on the 28-point gait/axial MDS-UPDRS subscale, would be clinically significant. For comparison, the estimated minimum clinically important change on the full 132-point MDS-UPDRS motor scale is ≈2% (2.5 points).^43^ Furthermore, the axial-gait items of the MDS-UPDRS are those with the greatest impact on quality of life.^42^

As this is an early-phase proof of concept trial, it is important to maximise the chances of continuing development if the treatment is genuinely effective, and thus a significance level of 25% under a one-sided test will be used. If the treatment effect is a 2% change (0.37 standardised effect), the design has 78% power, and for a 4% change (0.73 standardised effect), the design has 99% power.

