### Treatment allocation, blinding and safety monitoring

Participants will be randomised 1:1 to receive azathioprine or placebo using Sealed Envelope, an online randomisation system. Clinical assessors and participants will be blinded to treatment allocation. Balanced assignment of each treatment will be achieved using permuted block randomisation, which will be stratified for: age ≤71 versus >71, and MDS-UPDRS-III ≤30 versus >30.

Treatment will be commenced at a dose of 1 mg/kg, based on 25 mg tablets of IMP (azathioprine/placebo). In addition to the visits shown in figure 1, treatment monitoring visits will be conducted to screen for potential complications associated with azathioprine. These will include blood tests to screen for myelosuppression, liver or renal dysfunction, AEs reporting and assessment of treatment compliance (review of patient-completed dosing diary and counting of the investigational medicinal product (IMP) at regular intervals). Initially, monitoring visits will occur 2 weekly, and after 4 weeks, the azathioprine dose will be increased to 2 mg/kg (assuming blood tests and clinical assessments are satisfactory), the standard therapeutic dose used in clinical practice. There will be a matched doubling of the placebo dose to maintain blinding. Once the participant is stable on their dose, treatment monitoring will be carried out less frequently (see monitoring protocol, figure 3).

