**Figure 3 F3:**
[figure not shown]
Treatment monitoring schedule.

Given that azathioprine will produce changes in FBC parameters, the blinded trial team conducting patient assessments and laboratory analysis will not have access to monitoring blood results throughout the duration of the trial. The blood tests will be reviewed by a separate unblinded team of clinicians, who will make decisions on dose changes when necessary. If a dose reduction is required, the participant will have an additional three monitoring visits at 2-weekly intervals to ensure stability of blood tests. Dose reductions and, where necessary, withdrawal of treatment will be carried out based on predefined clinical and laboratory criteria to ensure the safety of participants, including the development of significant myelosuppression, intolerable gastrointestinal side effects and hypersensitivity reactions. Participants who have been withdrawn from treatment will be encouraged to continue to attend the remainder of the trial assessments.

To ensure blinding is maintained among clinical assessors and participants, dose adjustments and treatment withdrawals will be also made for an equal number of participants in the placebo arm, with additional monitoring visits. Matched pairs of placebo and azathioprine-treated participants will be generated to facilitate this, and all dose adjustment decisions will be made by the unblinded team.

Emergency unblinding will be carried out in the event of a valid medical or safety reason, where the clinical care of the participant will be facilitated by the knowledge of whether they have been taking azathioprine, as decided by the treating clinician. It will be executed using Sealed Envelope, and where possible, the trial team will remain blinded.

Following the end of the trial, and for participants who withdraw early, we will offer continuing follow-up through our research clinic at the VGB.

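### The stated powers belong to changes of about 2.2% and 4.4% with all 60 patients evaluable; an exact 2% change has about 73% power, not 78%

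*Protocol article*

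**What the plan says.** The sample size calculation section of the protocol article says that the treatment effect is unknown, and that "A sample size of 60 has been selected pragmatically based on feasibility of recruitment". It then takes an anticipated effect from a cohort study stratified by cytokine profile. The mean (SD) annualised change in gait/axial score was 1.95 (1.92) in the proinflammatory group (n=32) and 0.72 (1.40) in the anti-inflammatory group (n=26). The difference is given as 1.2 points and a Cohen's d of 0.73, "which equates to a 4% change on the 28-point gait/axial MDS-UPDRS subscale". For comparison, the minimum clinically important change on the full 132-point motor scale is put at about 2% (2.5 points).

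On the test, "a significance level of 25% under a one-sided test will be used". On power, "If the treatment effect is a 2% change (0.37 standardised effect), the design has 78% power"; for a 4% change, labelled 0.73, the power is given as 99%.

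The section on treatment allocation, blinding and safety monitoring foresees withdrawal of treatment in some participants, with matched withdrawals on placebo. It adds: "Participants who have been withdrawn from treatment will be encouraged to continue to attend the remainder of the trial assessments". No rate of missing 12-month scores is given.

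**The concern.** The power sentence names each effect twice, as a percentage of the scale and as a standardised effect. The scale length (28 points) and the SDs are both printed, so the two descriptions can be checked against each other, and they differ. The standardised effects are about a tenth larger than the percentages imply.

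This matters most at the smaller effect. Two sentences earlier the text uses about 2% as its benchmark for a clinically important change. A reader will take 78% as the chance that the trial detects an effect of that size, and 22% as the chance that it misses one. The trial accepts a 25% one-sided error rate in order not to drop an effective drug, so the miss rate is the figure by which a negative result will be judged.

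**Working it through.** **Inputs (sample size calculation section, protocol article).** One-sided alpha 0.25; 60 patients randomised 1:1, so 30 per arm; cohort means 1.95 and 0.72; SDs 1.92 and 1.40; 28-point subscale; benchmark 2.5 of 132 points.

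**Step 1: recover the SD.**
- Difference: 1.95 − 0.72 = 1.23 points (printed as 1.2).
- Root mean square SD: √((1.92² + 1.40²)/2) = 1.680. Then 1.23/1.680 = 0.73, the printed value.
- The n-weighted pooled SD is 1.708 and gives 1.23/1.708 = 0.72, so 1.68 is taken as the plan's SD.

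**Step 2: reproduce the plan's powers.** Two-sample t-test, noncentrality d × √(30/2), 58 degrees of freedom, one-sided alpha 0.25.
- d = 0.37: noncentrality 1.433, power 77.5% (77.6% by the normal approximation). Stated: 78%.
- d = 0.73: noncentrality 2.827, power 98.4%. Stated: 99%; it rounds to 98%.

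The printed powers are therefore those of the printed standardised effects, with all 60 patients contributing a 12-month score.

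**Step 3: turn the standardised effects into points.**
- 0.37 × 1.68 = 0.62 points; 0.62/28 = 2.2%.
- 0.73 × 1.68 = 1.23 points; 1.23/28 = 4.4%.

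**Step 4: turn the percentages into standardised effects.**
- 2% of 28 = 0.56 points; 0.56/1.68 = 0.333.
- 4% of 28 = 1.12 points; 1.12/1.68 = 0.667.

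**Step 5: power at each description, 60 evaluable.**

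| Effect | Points | d | Power | Stated |
|---|---|---|---|---|
| 2.2% | 0.62 | 0.37 | 77.5% | 78% |
| exact 2% | 0.56 | 0.333 | 73.0% | 78% |
| 4.4% | 1.23 | 0.73 | 98.4% | 99% |
| exact 4% | 1.12 | 0.667 | 97.1% | 99% |

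With the SD of 1.708, an exact 2% change has 72.4% power.

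**Step 6: the benchmark itself.** 2.5/132 = 1.89%. Carried over to the 28-point scale, this is 0.53 points; 0.53/1.68 = 0.32, with about 71% power. The benchmark has been rounded up to 2%, while the powered effect has been rounded down to 2%. The two look equal, but 2.22/1.89 = 1.17, so the powered effect is about 17% larger.

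**Step 7: missing scores, for illustration only.** The document gives no rate. If 10% to 20% of 12-month scores were missing (54 to 48 evaluable), d = 0.37 would have about 75% to 73% power, before any gain from the planned ANCOVA.

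**The case against.** The strongest reply is that nothing has been miscalculated. Each power stands beside a standardised effect and reproduces from it to within a percentage point. The percentages are whole-number labels: 1.2 points is printed before the 4%, half of 1.23 is 0.615 points or 2.2%, and the benchmark is itself printed as approximate. On this reading the 78% is right for d = 0.37, and only the label is loose. That is correct as far as it goes, and it means that 78% should not be called a wrong power calculation. It does not rescue the sentence, because 2% is the figure that ties the power to the benchmark, and at that level the rounding is worth about 5 percentage points of power.

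The reply is fully right on the larger effect: 97% or 98% against 99% changes nothing. It is also right that 60 was not derived from these powers.

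A reader might go further and infer that the true power is 68% to 71%, because withdrawals are expected. The document does not support that. Those figures (exact 2%, 10% to 20% loss) need a loss rate that it does not give. The withdrawals it describes are withdrawals of treatment, with continued assessment encouraged and an intention-to-treat analysis, so a withdrawn patient need not lack a 12-month score. An attrition allowance may also stand in the full protocol. The planned ANCOVA, with baseline score, gender, LEDD and age, could recover some precision, and no credit is taken for it here.

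**Conclusion.** The point holds as a mismatch between labels and powers. The powers of 78% and 98% (printed as 99%) apply to about 0.62 and 1.23 points, that is 2.2% and 4.4% of the scale. An exact 2% change has about 73% power, and an effect equal to the unrounded benchmark about 71%. The chance of missing a benchmark-sized effect is therefore 27% to 29% (100 − 73 and 100 − 71), not the 22% that the text implies. The discrepancy at 4% is immaterial.

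These figures rest on the SD of 1.68 inferred from the printed d, an unadjusted two-sample comparison, and 60 evaluable patients. The arithmetic is firm; any further fall through missing scores is an assumption. The sample size, the significance level and the analysis are unaffected. What changes is how a negative result should be read.

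**What to change.** Make the two descriptions of each effect agree, in one of two ways:

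- keep the standardised effects and relabel them: 0.62 points (2.2%, d = 0.37) with 78% power, and 1.23 points (4.4%, d = 0.73) with 98%; or
- keep the percentages and correct the rest: 0.56 points (2%, d = 0.33) with 73% power, and 1.12 points (4%, d = 0.67) with 97%.

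The first keeps the cohort difference as the anchor. The second gives the power at the 2% level that the text compares with the minimum clinically important change. In either case, state the SD used and that 60 evaluable patients are assumed. If the team has an expected rate of missing 12-month scores, give the power for that number as well.

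The cost is a sentence or two and, under the second option, a slightly less favourable power figure. The number of patients stays at 60.

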### Trial procedures

#### Clinical

Clinical measures assessing both motor and non-motor components of PD will be performed at baseline, midtreatment, end of treatment and after 6-month further follow-up (see table 1). Throughout the course of the trial, participants will continue to take their PD medication as prescribed by their treating physician, and dose adjustments are permitted. However, some assessments will be conducted ‘OFF’ medication.

**Table 1 T1:** Schedule of assessments

	Screening visit	Imaging visit	CSF collection	Baseline visit	Monitoring visits*	Dose escalation visit	Midtreatment visit	End-of-treatment visit	Imaging visit	Follow-up visit
	Day −42 (max)	Approx. day −14±	Approx. day −7±	Day 0±14	Day 14±5 and onwards	Day 28±5	Day 182±14	Day 365±14	Day 410±45	Day 547±14
Informed written consent	✓									
Eligibility review	✓									
Randomisation				✓						
Vital signs				✓	✓	✓	✓	✓		✓
Weight in kg	✓			✓	✓	✓	✓			
Clinical assessments										
Demographics				✓						
Medical history	✓			✓	✓	✓	✓	✓		✓
Concomitant medication review	✓			✓	✓	✓	✓	✓		✓
MDS-UPDRS				✓			✓	✓		✓
NART				✓						
ACE-III				✓			✓	✓		✓
GDS				✓			✓	✓		✓
NMSS				✓			✓	✓		✓
PDQ-39				✓			✓	✓		✓
Adverse events review	✓	✓	✓	✓	✓	✓	✓	✓	✓	✓
IMP compliance check					✓	✓	✓	✓		
Imaging – optional										
(11C)-PK11195 PET-MRI		✓							✓	
Blood tests										
Screening bloods†	✓									
Safety monitoring bloods‡					✓	✓	✓	✓		✓
CRP, immunoglobulins and serum storage for cytokine measurement			✓				✓	✓		✓
Immunophenotyping			✓					✓		✓
CSF – optional										
Immune markers and immunophenotyping			✓					✓		

*Monitoring visits will take place at: day 14, day 42, day 56, day 70, day 98, day 252 and day 547 (as part of the routine follow-up visit). Additional monitoring visits may also be scheduled if there are patient safety concerns.

†Screening bloods include FBC, U&Es, LFTs, coagulation, TPMT, HIV, syphilis, hepB, hepC, EBV serology, VZV serology, LH and FSH (if female and reproductive age).

‡Monitoring bloods include FBC, U&Es and LFTs.

ACE-III, Addenbrooke’s Cognitive Examination-III; CRP, C reactive protein; CSF, cerebrospinal fluid; EBV, Epstein-Barr virus; FBC, full blood count; FSH, Follicle-stimulating hormone; GDS, Geriatric Depression Scale; HepB, Hepatitis B; HepC, Hepatitis C; IMP, Investigational medicinal product; LFT, liver function tests; LH, Luteinising hormone; MDS-UPDRS, Movement Disorder Society-Unified Parkinson’s Disease Rating Scale; NART, National adult reading test; NMSS, Non-Motor Symptom Scale; PDQ-39, Parkinson’s Disease Questionnaire 39; PET, positron emission tomography; TPMT, Thiopurine methyltransferase; U&E, urea and electrolytes; VZV, Varicella zoster virus.

The MDS-UPDRS is widely used to quantify PD severity and includes questionnaires assessing the non-motor and motor aspects of the disease, a motor examination performed by a clinician and an assessment of motor complications (dyskinesias and fluctuations).^44^ The MDS-UPDRS part III will be assessed in the OFF state, in the absence of regular dopaminergic medication, with participants being asked to not take their levodopa in the 8 hours prior to the assessment or their long-acting agents (eg, ropinirole, pramipexole and rasagiline) in the preceding 36 hours. The aim of this is to expose underlying disease severity and avoid confounding effects from variability in medication doses or timing. This examination will be filmed to enable subsequent rating by an independent assessor to check inter-rater reliability. Our primary outcome measure is derived from the MDS-UPDRS: the gait/axial subscore, as previously discussed. Two sections of the MDS-UPDRS part III (tremor and bradykinesia) will be repeated while the participant is wearing an EMS (Polhemus Inc) on the index finger and thumb, which will give an objective measure of the participant’s movements. Motor stage will also be evaluated using the Hoehn and Yahr scale, a five-point scale used to capture the stages of progression of PD, with stage 3 representing the development of postural instability.^45^

Cognition will be assessed using the ACE-III. This provides a global measure of cognition as well as subscores in five domains; attention, memory, fluency, language and visuospatial function.^46^ Other non-motor aspects of PD will be evaluated using the short form 15-item Geriatric Depression Scale, a questionnaire assessing depressive symptoms filled in by the participant,^47^ and the PD NMSS, completed by the trial assessor.^48^ Finally, we will use the PDQ-39, a self-rated questionnaire measuring PD-related quality of life.^49^

Dopaminergic medication requirement will be monitored throughout the trial and standardised by calculating LEDD, which allows quantification of different doses and types of Parkinson’s medication on a single scale.^50^

#### PK-11195 PET imaging

[^11^C]-PK11195 PET will be used to measure activated microglia in the brain.^17 18^ Scanning will be conducted at the Wolfson Brain Imaging Centre (WBIC) on a GE SIGNA PET/MRI scanner, with the radiotracer produced at the WBIC Radiopharmaceutical Chemistry laboratory. MRI will be used for colocalisation. Five hundred megabecquerel of the[^11^C]-PK11195 radiotracer will be injected via a peripheral venous cannula over 30 s, and PET emission data will be acquired for 75 min postinjection in 55 time frames. Following image reconstruction and attenuation correction, specific tracer binding will be analysed with the simplified reference tissue model^51^ to quantify binding potential relative to a non-displaceable compartment (BP_ND_). The reference region will be estimated with supervised cluster analysis for [^11^C]PK11195 from existing scans in healthy controls acquired on the same scanner. BPND will be compared pretreatment and post-treatment using a region of interest approach.

Given that some participants may have difficulty tolerating prolonged PET imaging, this will be optional. It will be performed between screening and baseline and repeated within 3 months following the end of treatment.

### Biosample collection and processing

Fourteen millilitres of blood will be collected in serum tubes at baseline, midtreatment, end-of-treatment and follow-up visits for analysis of inflammatory cytokines, C reactive protein and immunoglobulins. Tubes will be centrifuged at 2000 RPM (600G) for 15 min following 15 min clotting time for extraction of serum. Aliquots will be stored at −80°C for subsequent batch analysis using ELISA and electrochemiluminescence assays.

At baseline, end of treatment and follow-up visits, an additional 27 mL of blood will be collected in lithium heparin tubes for separation of peripheral blood mononuclear cells (PBMCs) for immunophenotyping. A concurrent full blood count (FBC) will be performed from an EDTA sample (2.6 mL).

CSF will be collected via lumbar puncture before the baseline visit and at the treatment endpoint. This is an optional component of the study in order to ensure that its inclusion does not limit recruitment. CSF will be spun at 400G for 10 min for extraction of immune cells for contemporaneous immunophenotyping alongside PBMC analysis. Supernatants will be stored at −80°C for later batch analysis of relevant immune and protein markers. Immunophenotyping will be performed for subsets of T cells, B cells and monocytes using flow cytometry, run within 24 hours of sample collection.

### Treatment allocation, blinding and safety monitoring

Participants will be randomised 1:1 to receive azathioprine or placebo using Sealed Envelope, an online randomisation system. Clinical assessors and participants will be blinded to treatment allocation. Balanced assignment of each treatment will be achieved using permuted block randomisation, which will be stratified for: age ≤71 versus >71, and MDS-UPDRS-III ≤30 versus >30.

Treatment will be commenced at a dose of 1 mg/kg, based on 25 mg tablets of IMP (azathioprine/placebo). In addition to the visits shown in figure 1, treatment monitoring visits will be conducted to screen for potential complications associated with azathioprine. These will include blood tests to screen for myelosuppression, liver or renal dysfunction, AEs reporting and assessment of treatment compliance (review of patient-completed dosing diary and counting of the investigational medicinal product (IMP) at regular intervals). Initially, monitoring visits will occur 2 weekly, and after 4 weeks, the azathioprine dose will be increased to 2 mg/kg (assuming blood tests and clinical assessments are satisfactory), the standard therapeutic dose used in clinical practice. There will be a matched doubling of the placebo dose to maintain blinding. Once the participant is stable on their dose, treatment monitoring will be carried out less frequently (see monitoring protocol, figure 3).

**Figure 3 F3:**
[figure not shown]
Treatment monitoring schedule.

Given that azathioprine will produce changes in FBC parameters, the blinded trial team conducting patient assessments and laboratory analysis will not have access to monitoring blood results throughout the duration of the trial. The blood tests will be reviewed by a separate unblinded team of clinicians, who will make decisions on dose changes when necessary. If a dose reduction is required, the participant will have an additional three monitoring visits at 2-weekly intervals to ensure stability of blood tests. Dose reductions and, where necessary, withdrawal of treatment will be carried out based on predefined clinical and laboratory criteria to ensure the safety of participants, including the development of significant myelosuppression, intolerable gastrointestinal side effects and hypersensitivity reactions. Participants who have been withdrawn from treatment will be encouraged to continue to attend the remainder of the trial assessments.

To ensure blinding is maintained among clinical assessors and participants, dose adjustments and treatment withdrawals will be also made for an equal number of participants in the placebo arm, with additional monitoring visits. Matched pairs of placebo and azathioprine-treated participants will be generated to facilitate this, and all dose adjustment decisions will be made by the unblinded team.

Emergency unblinding will be carried out in the event of a valid medical or safety reason, where the clinical care of the participant will be facilitated by the knowledge of whether they have been taking azathioprine, as decided by the treating clinician. It will be executed using Sealed Envelope, and where possible, the trial team will remain blinded.

Following the end of the trial, and for participants who withdraw early, we will offer continuing follow-up through our research clinic at the VGB.

### Trial monitoring and oversight

Safety monitoring will be overseen by a DSMB who will have access to interim recruitment and safety data. The DSMB will report to the TSC should it become clear that one treatment allocation is either indicated or contraindicated, or apparent that no clear outcome can be obtained from the trial. The TSC, who are independent from the sponsor, will provide overall supervision of the trial and ensure that it meets appropriate standards. These groups include clinicians with experience in PD or immunosuppression and independent statisticians, and the TSC includes a lay member.

AZA-PD is jointly sponsored by Cambridge University Hospitals Natioanl Health Service Foundation Trust and the University of Cambridge. The sponsor will review all trial documentation, including any proposed amendments, prior to submission to the relevant regulatory bodies, which can only be completed once the sponsor has approved the changes. Changes will then be communicated to participants, the DMSB, TSC and trial registries.

Adherence to the protocol and regulatory requirements will be reviewed by a Clinical Trials Monitor, assigned by the sponsor. The first monitoring visit will occur within 10 days of the first randomisation, with frequency thereafter determined by a risk assessment, which will be reviewed and adjusted as necessary throughout the course of the trial.

